## Experimental arm (CFT)

CFT is an experiential therapy. As such, in addition to psychoeducation components (e.g., compassion from an evolutionary and neuroscientific perspective, the tricky brain problem, emotion regulation systems) and explicit learning of emotion regulation skills (in particular, shame), experiential exercises are provided in-sessions (e.g., chair work, role plays, guided mental imagery) and in-between session practices will be provided with video guides, made available for the participants online (e.g., soothing rhythm breathing, safe place imagery, compassionate self-imagery). The overall aim of the CFT program is to help participants shift from a hostile and critical self-to-self relationship to a more compassionate relationship to self. To increase compassion for self, others and the ability to receive compassion from others, the CFT therapist guides patients to develop feelings of warmth, safeness, and soothing through compassionate mind training [32]. To do so, an integral part of CFT involves learning about brain functioning, specifically the roles of three emotion regulation systems: (i) the threat detection and protection system, (ii) the drive system, and (iii) the soothing and social safety system [32]. CFT proposes that psychological difficulties arise when the three emotional regulation systems are out of balance. Compassionate mind training strengthens the soothing system which can then regulate the threat and drive systems [52].

## Active control arm (psychoeducation-ESS)

ESS sessions cover topics such as the path from public stigma to self-stigma and modifying self-stigmatizing thoughts through cognitive restructuring techniques. Participants will be encouraged to do home practices (e.g., writing about the pros and cons of self-stigmatizing thoughts) between sessions.

Tables 1 and 2 show the detailed descriptions of CFT and ESS programs.

**Table 1 Tab1:** Title, content of sessions, and home practices of the CFT program (experimental arm)

**Session number**	**Session title**	**Session content**	**Home practice**
**1**	Welcoming and creating a safe place Definition of compassion and personal goals	• Introducing members of the group and therapists • Collective reflection on a safe place agreement for the group • Exercise: step in/me too • Exploration of what is (and what is not) compassion • Identification of personal objectives for the therapy • Short introducing to soothing rhythm breathing (SRB)	Soothing rhythm breathing (SRB) https://youtu.be/Md2c0h6bogE)
**2**	Compassion wisdom: the tricky brain and the social construction of self	• SRB • Tricky brain problem • How and why we are different to other animals: our unique capacity for self-consciousness and self-judgment (“not our fault”) • We are only one version of the infinite possible versions of self • Understanding the influence of our social environment on our construction (“not our fault”)	Soothing rhythm breathing (SRB) Identifying my own tricky brain loops
**3**	Compassion wisdom: three emotional regulation systems	• SRB • Introducing the three circles model: threat, drive, and soothing • Evolutionary function of emotions	Soothing rhythm breathing (SRB) Drawing my three circles and identifying triggers
**4**	Compassion wisdom: stigma and self-stigma	• SRB • Introduction stigma and self-stigma • Understanding the path from public stigma to self-stigma (“not our fault”) through the social construction of self and the tricky brain • Consequences of self-stigma through the lens of the 3-circle model	Soothing rhythm breathing (SRB) Filling the self-stigma model and tricky brain loops associated
**5**	Compassionate engagement: thinking, imagery, and body postures can influence our physiology	• SRB • Introducing the mindfulness circle • Thoughts and imagination can impact our physiology: experiencing with attention, postures, tones of voice, SRB • Safe place imagery • Ideal compassionate other imagery	Safe place imagery https://youtu.be/Md2c0h6bogE
6	Compassionate engagement: the compassionate self	• Experiencing with the compassionate self (postures, tone of voice, feelings of warmth, actions)	Compassionate self-imagery https://youtu.be/1KELVnBvvho
7	Compassionate courage: multiple selves	• Embodying the compassionate self to respond to the threat system thoughts and emotions	Compassionate self-imagery https://youtu.be/1KELVnBvvho
**8**	Compassionate courage: how to respond to the self-stigmatizing self	• Exploration of self-stigma and self-critic: reasons to be and consequences • Using compassionate self to respond to self-stigma	Compassionate self-imagery https://youtu.be/1KELVnBvvho
**9**	Compassionate courage: dealing with difficult emotions	• Understanding of shame and guilt • Responding to difficult emotions with compassion	Embodying compassionate self in everyday life
**10**	Compassionate courage: compassionate assertiveness	• Understanding the components of compassionate assertiveness compared to submissive and aggressive expression • Practicing compassionate assertiveness through role plays	Compassionately asking something we need
**11**	Compassionate courage: cultivating the compassionate self	• Writing a compassionate letter • Sharing of compassionate letters	Compassionate letter
**12**	Continuing my journey with compassion	• Reflection on the last 12 weeks • Building my personal compassionate tool bag • Plans for continuing practicing compassion • Gratefulness and compassion wish

**Table 2 Tab2:** Title, content of sessions, and home practices of the pychoeducation-ESS program (active control arm)

**Session number**	**Session title**	**Session content**	**Home practice**
**1**	What is stigma regarding mental illness, where does it come from; what are its impacts?	Self-reflections regarding stigma. Myths and facts about mental illness	Identifying negative ideas and assumptions about mental illness
**2**	What is internalized stigma and what are its impacts?	Self-reflections regarding internalized stigma Common stereotypes and their connections to internalized stigma	Identifying negative ideas and assumptions about myself linked to my mental illness
**3**	“Automatic thoughts” as part of internalized stigma	The 3C’s strategy to ameliorate/challenge them, part 1: catch it	Catching automatic thoughts
**4**	Completing the 3C’s strategy	Part 2: check it and change it. The thoughts behaviors-feelings cycle and internalized stigma	The 3C practice: catch, check, change
**5**	Importance of and strategies for strengthening yourself	“Growing” the positive aspects of yourself that you may have put on the back burner due to mental illness and other challenges	Facets of myself Reclaiming and strengthening parts of my true self
**6**	Increasing belonging	Part 1: the importance of belonging and positive connections with others in staying strong, resisting internalized stigma, enhancing quality of life, and reducing alienation	Adding to belonging: identifying: activity, value, interest
**7**	Increasing belonging	Part 2: practical strategies for increasing belonging	Adding to belonging: next steps
**8**	Increasing belonging	Part 3: the importance of and strategies for optimizing relationships with family and close friends. Increasing the positive, reducing the negative, taking care of oneself to enjoy the former, and tolerate the latter	Increasing belonging with family and friends
**9**	Responding to stigma, disrespect, or discrimination from others	Part 1: in ways that do not lead to internalized stigma, revisiting the thoughts feelings-behaviors cycle	Managing discrimination related to mental illness
**10**	Responding to stigma, disrespect, or discrimination from others	Part 2: cognitive and behavioral strategies	Managing discrimination related to mental illness
**11**	Course recap	Summary of each session and its accompanying strategies	My tools and strategies
**12**	Next steps	Crafting an action plan for after the class. Course evaluation	

## Passive control arm (TAU)

Participants will not participate in any intervention aimed at reducing self-stigma. They will continue their usual treatment which might include weekly visits to their psychiatrist. Participants and therapists in each center will receive, after the study period, access to the ESS notebook.

### Criteria for discontinuing or modifying allocated interventions {11b}

Participants may withdraw their consent and request to leave the study at any time for whatever reason. The investigator must document the reasons for early discontinuation as fully as possible. The investigator has the right to discontinue a subject’s participation in the study, temporarily or permanently, for any reason that is in the best interest of the subject.

Participants who prematurely discontinue the study procedure will continue follow-up in the study until the end-of-study visit scheduled in the protocol. The criteria for premature termination of participation by the investigator are long-term hospitalization (more than 1 month).

For patients in the three arms, in case of premature termination of participation in the study by decision of the investigator or the patient/guardian, the self-report questionnaires including the ISMI will be administered one last time to the exiting participant, if the patient/guardian agrees. A semi-structured evaluation interview will also be conducted.

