### Randomization

The investigator (psychiatrist) will then confirm the eligibility of the patient to another investigator (psychologist or nurse) of their team, who will be in charge of the randomization of the patients on the CleanWEB platform. This will ensure a blind assessment of the post-treatment evaluation by the psychiatrist at V1 and V2 (i.e., the BPRS and Mini-FROGS scales).

Patients will be randomized by the psychologist or the nurse into one of the following arms:Experimental arm: 12 week-treatment of compassion-focused therapy (CFT) (i.e., psychoeducation on the model, experiential in-session exercises, and in-between session compassion practices, video-guided practices). Sessions cover several topics: psychoeducation on compassion from an evolutionary and neuroscientific perspective, emotion regulation skills (especially shame), and compassion practices.Active control arm: 12 week-treatment of the psychoeducation program *Ending Self-Stigma* (ESS) [29]. Sessions cover topics such as modifying self-stigmatizing thoughts and homework.Passive control arm: patients follow their usual care, i.e., TAU (e.g., psychiatric, psychological, day hospital), which will be unchanged during the 12-week period. Following their 10-month participation in the study, they will be given access to the written material used for the ESS.

Participants will then be asked to complete self-report questionnaires assessing self-compassion, shame, depression, anxiety, barriers to care, social functioning, recovery, and functional remission. During this visit, the cognitive task assessing avoidance/approach attitudes toward mental illness (VAAST) will also be carried out by the psychologist or the nurse.

Two individual sessions with a clinician (engagement phase) will be conducted between V0 and the beginning of CFT and ESS (i.e., within 1 month). These sessions will include motivational interviewing techniques and case conceptualization aimed at increasing the participant’s level of engagement in therapy.

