### Follow-up visit V1 (end of treatment + 1 week)

This visit corresponds to the end-of-treatment assessment (T1) for patients in each arm, starting at week 18 after inclusion (following the last group session for the active arm and the active control arm). This evaluation includes the administration of the self-report questionnaires, including the ISMI, and the administration of the cognitive task (VAAST). A psychiatrist blinded to the experimental arm of the patient will conduct an evaluation of psychiatric symptoms and functional remission via the BPRS and the Mini-FROGS.

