### Follow-up visit V2 (end of treatment + 6 months)

This visit corresponds to the follow-up assessment (T2) for patients of each arm, starting 6 months after the last group treatment session (and 9 months after the inclusion of the TAU group). This evaluation includes the administration of the self-report questionnaires, including the ISMI, the administration of the cognitive task (VAAST). A psychiatrist blinded to the experimental arm of the patient will conduct an evaluation of psychiatric symptoms and functional remission via the BPRS and the Mini-FROGS**.**

Moreover, in the Strasbourg center only, a semi-structured interview will be led by a clinical psychologist blinded to the experimental arm of the patient (i.e., a clinical psychologist not involved in the trial to make sure that they had no previous contact with the participant). The interview will assess the avoidance of participants (due to self-stigma) in several social situations as well as their satisfaction with the intervention (CFT and ESS).

An additional 1-month window will be allowed to conduct this visit. The participation of patients ends at the end of this visit (Fig. 1). Table 3 shows the schedule for the COMPASS study.

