### Plans to promote participant retention and complete follow-up {18b}

Patients enrolled in the study will receive a compensation (i.e., 100 euros) at the end of the last visit with the psychiatrist. To receive the compensation, participants must have completed the visits V1, V2, and V3.

For patients in the three arms, in case of premature termination of participation in the study by decision of the investigator or the patient/guardian, the self-report questionnaires including the ISMI will be administered one last time to the exiting participant, if the patient/guardian agrees. A semi-structured evaluation interview will also be conducted. For patients who quit the study prematurely, all data collected before the decision to interrupt the study will be analyzed.

A participant starting psychotherapy in parallel to their participation in the protocol will be kept in the group for ethical and clinical reasons. Their data will be excluded from the study.

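### Hospitalization of more than 1 month is best read as ending study participation, so V1 and V2 visits still due may be lost after an event that can be related to outcome

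*Protocol article*

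**What the plan says.** Section {11b} of the protocol article describes two situations in adjacent sentences.

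- Stopping the study procedure: "Participants who prematurely discontinue the study procedure will continue follow-up in the study until the end-of-study visit scheduled in the protocol".
- Termination by the investigator: "The criteria for premature termination of participation by the investigator are long-term hospitalization (more than 1 month".

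The paragraph that follows covers premature termination of participation by decision of the investigator or the patient, in all three arms. It provides that "the self-report questionnaires including the ISMI will be administered one last time to the exiting participant, if the patient/guardian agrees", and adds a semi-structured interview whose content is not described. Section {18b} repeats this and adds: "For patients who quit the study prematurely, all data collected before the decision to interrupt the study will be analyzed".

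Section {11b} also lets the investigator discontinue a subject for a time or for good where that serves the subject's interest.

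The V1 section places that visit "starting at week 18 after inclusion", and a blinded psychiatrist "will conduct an evaluation of psychiatric symptoms and functional remission via the BPRS and the Mini-FROGS". The V2 section places the second visit "starting 6 months after the last group treatment session (and 9 months after the inclusion of the TAU group", with the same blinded ratings. Section {20c} announces an intention-to-treat analysis in order to limit attrition bias.

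**The concern.** A long hospital stay occurs after randomization and, in people with severe mental illness, can plausibly be related to symptoms, functioning and self-stigma. If it ends participation, the trial stops observing patients because of an event that may itself be related to outcome. That works against the intention-to-treat aim, and against the principle in the same paragraph that people who stop the procedure stay in follow-up.

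The criterion is limited neither to the weeks with sessions nor to the active arms. A TAU patient, or a patient in any arm admitted between V1 and V2, has no trial sessions left to stop. For them, termination can only remove visits.

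The exit step is a partial substitute. The self-reports need agreement and have no scheduled date, and the article does not say that the step includes the blinded BPRS or Mini-FROGS. Those ratings have particular value because the ISMI is self-reported by participants who know their arm.

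**Working it through.** **1. Which reading fits the text.** The criterion and the exit paragraph share one term, premature termination of participation by the investigator. The exit paragraph speaks of someone leaving and of a final administration of the ISMI. That does not fit a patient who still has the ISMI due at V1 and V2. It also applies to all three arms, and TAU has no programme to stop. The stricter reading is therefore the better one, but it remains an inference.

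**2. The plan's own allowance for loss.** From Sample size {14}: 84 x 1.33 = 111.7, so 112 per arm, and 3 x 112 = 336. The stated figures are reproduced. The allowance is 112 - 84 = 28 per arm, or 28/112 = 25%. It is not split by cause.

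**3. Share of patient-time with sessions.** Inputs:

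- 12 weeks of sessions in two of three arms: 84 days / 30.44 = 2.76 months.
- An engagement phase of up to 1 month before the sessions.
- V2 six months after the last session; for TAU, 9 months after inclusion.
- 10 months in total according to the Randomization section ("Following their 10-month participation in the study, they will be given access to the written material used for the ESS"), taken here to apply to all arms.

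Results:

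- Low share (group sessions only, 10 months in every arm): 2 x 2.76 / (3 x 10) = 5.52/30 = 18%.
- High share (the whole engagement month counted as sessions): active arms 1 + 2.76 + 6 = 9.76 months, TAU 9 months; 2 x 3.76 / (2 x 9.76 + 9) = 7.52/28.52 = 26%.
- Without sessions: about 74% to 82%.

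This pools TAU, which has no sessions by design. In the active arms alone, group sessions fill 12/43.5 = 28% to 12/38.1 = 32% of the time (participation of 43.5 and 38.1 weeks), so 68% to 72% has none.

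**4. Which visit is more exposed.** One month is 4.35 weeks.

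- To be terminated before V1, an admission must start by about week 18 - 4.35 = 13.7.
- To be terminated before V2 at 9 to 10 months, it can start until month 8 to 9, that is week 34.8 to 39.1.
- The V1 window is 13.7/39.1 = 35% to 13.7/34.8 = 39% as long as the V2 window. Whoever is terminated before V1 loses V2 as well.

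**5. Possible size of bias, under assumptions.** The documents give no hospitalization rate. If a share p of an arm is removed, and those removed differ by d from those kept, the mean of those kept differs from the full-arm mean by p x d. With the same d in both arms, the shift in the arm contrast is (difference in p) x d. Assume the shares differ by 0 to 2 percentage points (0.02 x 112 = 2.2, about 2 patients) and d is 0 to half a planned SD.

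| Visit | Half SD | Maximum shift | Relative to planned difference |
|---|---|---|---|
| V1 | 0.41/2 = 0.205 | 0.02 x 0.205 = 0.0041 | CFT-ESS 0.10: 4.1%; CFT-TAU 2.43 - 2.10 = 0.33: 1.2% |
| V2 | 0.48/2 = 0.24 | 0.02 x 0.24 = 0.0048 | CFT-ESS 2.40 - 2.20 = 0.20: 2.4% |

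The direction can be either way. If half of the exits give a usable ISMI, the maxima fall to about 0.0020 and 0.0024. If shares and d are equal across arms, the shift is zero.

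**The case against.** The strongest defence is that nowhere does the article say that V1 or V2 is cancelled after a long hospitalization. The section concerns allocated interventions, the preceding sentence keeps people in follow-up, and discontinuation may be temporary and is the investigator's decision. A patient discharged after five weeks could be paused and attend later visits. This stands as a real alternative reading. It does not settle the matter, because it sits badly with the exit wording and gives TAU patients nothing to stop. Two adjacent sentences that seven centers may apply differently need the same clarification.

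A reader might infer from {18b} that data after the decision are discarded. The text does not say that: it secures the data collected before the decision and does not forbid later visits. It does leave unclear how an ISMI taken at exit, after the decision, would be used. A reader might also infer that the BPRS and Mini-FROGS are certainly omitted at exit. They are not among the self-reports, but the content of the exit interview is not described, so that cannot be asserted.

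It is also fair that {14} allows for 28 losses per arm, and that {20c} keeps anyone with at least one value and plans multiple imputation at 3% to 20% missing. The complete-case shift above is therefore an illustration and not generally the planned estimator. Some visits would be missed under any rule, because of constraint, distance or clinical state.

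**Conclusion.** The point holds as a weakness in conduct, with medium confidence. The hospitalization criterion is best read as ending visits still due in all three arms. About 74% to 82% of pooled patient-time has no trial sessions, so for much of the trial the rule can remove follow-up without stopping any treatment. That share describes planned time; it becomes a share of admissions only if admissions are spread evenly, which the documents do not state.

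A reader might infer that the primary result is materially biased. The documents do not support that. No hospitalization rate is given, the number affected may be small, and the bias may be zero. Under the stated assumptions it is at most about 4% of the planned CFT-ESS difference at V1 and about 2% at V2. The main cost is avoidable missing visits, chiefly at V2, which carries the maintenance objective, and possibly the loss of blinded ratings.

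**What to change.** State in {11b}, and in line with it in {18b}, that:

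- hospitalization of more than 1 month may stop or pause the allocated intervention but does not end follow-up;
- V1 and V2 are attempted at their scheduled dates, with at least the ISMI and the other self-reports, plus the BPRS and Mini-FROGS where the blinded psychiatrist can reach the patient;
- the exceptions are withdrawn consent, and care under constraint or a clinical state that prevents the visit;
- any exit ISMI is analysed at its actual date and is not treated as V1 or V2.

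This is a short amendment that extends a follow-up principle already stated in the same paragraph. It changes neither the sample size nor the analysis model. The cost is a few ward or delayed visits, some of them not feasible, and some extra work for the blinded psychiatrist.

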### Strategies to improve adherence to interventions {11c}

Supervision sessions will be held monthly with the Strasbourg team to increase adherence to the psychotherapy models. Moreover, ESS clinicians will not deliver CFT (and vice versa) in order to increase adherence.

Members of the Strasbourg team will participate in monthly supervision sessions with the developers of ESS and group CFT expert clinicians to increase adherence.

Treatment fidelity checks (via fidelity tracking sheets) will be conducted by observers (e.g., graduate-level psychology students) to ensure reliable delivery of treatment and make further replication possible.

